## Abstract

**Background:**

Prevention of falls in the elderly is a public health target in many countries around the world. While a large number of trials have investigated the effectiveness of fall prevention programs, few focussed on interventions embedded in the general practice setting and its related network. In the Prevent Falls (PreFalls) trial we aim to investigate the effectiveness of a pre-tested multi-modal intervention compared to usual care in this setting.

**Methods/Design:**

PreFalls is a controlled multicenter prospective study with cluster-randomized allocation of about 40 general practices to an experimental or a control group. We aim to include 382 community dwelling persons aged 65 and older with an increased risk of falling. All participating general practitioners are trained to systematically assess the risk of falls using a set of validated tests. Patients from intervention practices are invited to participate in a 16-weeks exercise program with focus on fall prevention delivered by specifically trained local physiotherapists. Patients from practices allocated to the control group receive usual care. Main outcome measure is the number of falls per individual in the first 12 months (analysis by negative binomial regression). Secondary outcomes include falls in the second year, the proportion of participants falling in the first and the second year, falls associated with injury, risk of falls, fear of falling, physical activity and quality of life.

**Discussion:**

Reducing falls in the elderly remains a major challenge. We believe that with its strong focus on a both systematic and realistic fall prevention strategy adapted to primary care setting PreFalls will be a valuable addition to the scientific literature in the field.

**Trial registration:**

NCT01032252

## Background

Among elderly people falls are a major health problem associated with significant morbidity and economic burden. Based on the available data it is estimated that about 30% to 40% of community-dwelling older persons experience at least one fall per year with a high proportion falling more often than once [1-3]. These figures might be even underestimates. As patients and physicians consider falling and gait disorders as rather normal in older persons it is likely that there is a considerable underreporting of falls [4,5]. Major problems associated with falls include injury and fracture, reduced mobility, fear of falling, depression, admission to long-term care, decreased quality of life and death [6,7]. In Germany, about 125.000 persons per year suffer of mostly fall-induced hip fractures causing treatment costs of approximately 1.5 - 2 billion Euro [8,9]. Also, falls have a major role in about 26% of admissions to nursing homes leading also to major long term costs [10-12]. Lasting functional impairment occurs in 50% of fall patients with a hip fracture and 10% to 20% need permanent care [13]. Furthermore, psychological consequences such as fear of falling induce a negative vicious circle due to restriction of physical activities, thus decreasing quality of life and accelerating the process of functional decline of the aging process [14,15]. Given the demographic changes in many countries the prevalence of fall-related problems is likely to further increase in future [1,9].

A large number of clinical trials have investigated strategies to prevent falls or injurious falls. These studies have been summarized in several systematic reviews [3,10,16,17]. The recently published Cochrane review by Gillespie et al. focussing on fall prevention among older people living in the community includes 111 randomised controlled trials with a total of 55,303 participants [2]. There is some evidence for multiple-component group exercises, Tai Chi and individually prescribed multiple-component home-base exercises to reduce risk of falling and rate of falls [2,18]. Assessment and multifactorial intervention reduces rate of falls, but not significantly the general risk of falling [2,19-21]. Home safety interventions do not considerably reduce falls, but were effective in people with severe visual impairment and in others at higher risk of falling [2,22]. Also, anti-slip shoe device reduced rate of falls in icy conditions [2,23]. Furthermore, a prescribing modification programme for primary care physicians significantly reduces risk of falling [2,24] and gradual withdrawal of psychotropic medication reduces rate of falls, but not significantly risk of falling [2,25].

The systematic reviews [2,16] raised some methodological concerns: "Falling" was not always clearly defined and many trials were not powered adequately to detect clinically relevant effects. Many studies reported either rate of falls or the number of fallers although the Prevention of Falls Network Europe (ProFaNE) recommends to report both [26]. The duration of follow up was criticized to last only 12 months or shorter. Furthermore, one review demands that future trials should also include measurements of quality of life [16].

Several current guidelines [5,27-29] recommend multifactorial risk assessment of falls and interventions tailored to an individual's risk factor profile as a primary treatment strategy. However, implementing such strategies is far from easy. According to a qualitative study elderly persons regard fall prevention advices as generally useful but not personally relevant [30]. The likelihood that they take up fall prevention activities depends strongly on the setting and the characteristics of the intervention offered [31]. Older people view their general practitioners as a very important source of health-related information and value their advice [32,33]. Therefore, general practitioners are in an ideal position to identify persons at risk, and to recruit and motivate them to adhere to fall prevention programs [34]. While a large number of trials have investigated the effectiveness of fall prevention programs few focussed on interventions embedded in the general practice setting and its related network [16].

### Objectives

The primary aim of PreFalls is to investigate whether the implementation of a multimodal intervention in the German primary care setting (general practitioners), consisting of 16 weeks of group exercise in combination with an individualized home training program will significantly reduce number of falls per individual and risk of falling in community-dwelling elderly with high risk of falls compared to usual care. The secondary aim is to explore effects on the incidence and frequency of fall-related injuries, on balance, strength and mobility, fear of falling and quality of life. For this study a fall is defined as "an unexpected event in which the participant comes to rest on the ground, floor or at a lower level" [26].

## Methods/Design

### Study design and randomization

PreFalls is a controlled multicenter prospective study with cluster random allocation of participating general practices to an experimental or a control group. The study is performed in two regions (greater Munich and Nuremberg areas) in Bavaria, southern Germany. Two randomisation lists are computer generated by a statistician otherwise not involved in the study. The lists are stored by the two regional study coordinators. After the definitive inclusion of a general practice into the study, the coordinator of the respective region calls the coordinator of the other region who, after registering the practice, hands out the allocation information.

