### Participating patients

The target population of the study are community-dwelling persons aged 65 years and older with a high risk of falls. To be included at least one of the following criteria has to be met (see section measurements for a detailed description of the tests): fall within the last 12 months, fear for falling [35], chair-stand-ups >10 sec. [36], Timed-up-and-go-Test >10 sec. [37,38], balance impairments measured by the three balance tests of the Guralnik short physical performance battery [36] or self-reported subjective balance deficits. Persons not living independently and patients suffering from physical or mental restrictions that do not allow participation in an exercise program or the assessment of risk of falling are excluded. Each participating practice is asked to recruit 10 to 15 patients. In case of problems with recruiting the regional coordinating team supports recruitment activities.

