## Discussion

Reducing falls in the elderly remains a major challenge. Falls are common in older persons and can cause notable decreases of quality of life due to fear of falling, restricted mobility and loss of autonomy as well as large costs for health care systems [1-3,50,51]. The available evidence suggests that currently available interventions to reduce falls have limited effectiveness and should target on risk population [2,16,17]. This could be due to the interventions themselves, however, it could also be that interventions were implemented and investigated in a suboptimal setting. Most fall prevention studies were planned in specialized settings. To reduce falls on a population-based level the question of the role of the general practitioners regarding the uptake of fall prevention programs by the "at risk person" still has to be further investigated. PreFalls focuses on the first health-system contact for elderly-their general practitioner. Already in the planning phase general practitioners were an important part of the interdisciplinary study team. The long-term relationship and the frequent contacts of general practitioners with their patients allow the efficient detection of persons who might be at high risk of falling. Trained staff members in the practices can support the physicians in using simple but well validated tests to reliably assess the risk. The multimodal intervention comprising group exercise in combination with an individualized home training program has been pre-tested successfully in another setting [40,41]. Local networks with trained physiotherapists or sport scientists have been set up to implement the intervention in a manner, which is both adequate and realistic for a primary care setting. From a methodological point of view it would have been preferable to randomize individual patients instead of practices, as this eliminates the possibility that recruitment processes in intervention and control practices differ. This has not been possible due to logistical reasons. While PreFalls is adequately powered to detect a clinically significant reduction in falls it is not powered to reliably detect potentially clinically relevant reduction of injurious falls, as the incidence of such events is comparably low. However, PreFalls follows current recommendations for fall prevention studies such as documenting both the number of persons falling and the number of falls per person. Careful measurement of quality of life and fear of falling is included, also monitoring of improvement in balance, body weight bearing, as well as motor coordination especially when performing activities of daily life.

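### Allocation is released when a practice is registered, with no step that fixes its patients first, which leaves a risk of differential recruitment between arms

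*Protocol article*

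**What the plan says.** Under Study design and randomization, the trigger for release is the entry of the practice: "After the definitive inclusion of a general practice into the study, the coordinator of the respective region calls the coordinator of the other region". It is this second coordinator who records the practice and then discloses its arm. No patient-level step is placed before that call.

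Under Participating patients, recruitment is the practice's task: "Each participating practice is asked to recruit 10 to 15 patients". Help is available: "In case of problems with recruiting the regional coordinating team supports recruitment activities". Eligibility is broad: "To be included at least one of the following criteria has to be met", and the list runs from timed tests to "self-reported subjective balance deficits". Among those excluded are "patients suffering from physical or mental restrictions that do not allow participation in an exercise program".

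The Discussion says that randomising individual patients would have been preferable because "this eliminates the possibility that recruitment processes in intervention and control practices differ". It adds that this was ruled out by logistics. It does not mention enrolling patients before a practice's arm is disclosed.

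**The concern.** The telephone call between regions conceals the next allocation from whoever admits a practice. It does not protect the later step, in which the practice selects and invites patients. If the arm is known by then, three decisions can be influenced by it: whom the practice approaches, whether a restriction is judged to rule out exercise, and whether the patient consents. The article's Background itself says that older people's willingness to take up fall prevention depends strongly on what is offered and in what setting.

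If those decisions are related to fall risk, the arms differ at baseline for reasons other than chance. A larger sample does not remove such a difference, and neither does a negative binomial model that contains only the arm and random effects. A lower-risk intervention arm would look like benefit. A higher-risk one would hide benefit.

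**Working it through.** **1. Is the order of steps supported?** No sentence says that patients are recruited after disclosure. The evidence is:

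- Release depends on inclusion and registration of the practice only (Study design and randomization).
- Practices, with help if needed, then find their patients (Participating patients). The regional team that helps presumably includes the coordinator who obtained the allocation.
- The Discussion's worry that recruitment could differ between intervention and control practices makes sense mainly if practices know their arm while recruiting. Had patient lists been closed before disclosure, recruitment could not respond to the arm.

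Recruitment with the arm known is therefore the most natural reading, though an inferred one.

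**2. Does cluster randomisation force this order?** The logistical reason in the Discussion is given against randomising individuals. The risk-assessment workshop and the baseline visit are common to both arms (Participating practices; Table 2). Nothing stated prevents enrolment and baseline testing before a practice's arm is disclosed.

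**3. How much could it matter?**

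Inputs from Sample size justification: 33% versus 20% with at least one fall in 12 months, 80% power, two-sided 5%, intracluster correlation 0.02, cluster size 10, 382 patients, balanced arms.

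*The plan's own figure.* Design effect = 1 + (10 − 1) × 0.02 = 1.18. The usual two-proportion formula gives 180 per arm, so 2 × 180 × 1.18 = 425, not 382. The plan used simulation software whose settings are not shown. The difference does not affect this point, and 382 is taken as given below.

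*Effective size.* 382 / 2 / 1.18 = 161.9 per arm.

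*Rejection rate with no treatment effect.* Let the arms' underlying risks be p1 = 0.33 and p2 = 0.33 − d, with mean p̄. The imbalance d is an assumption; the documents give no value for it.

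- SE0 = √[2p̄(1 − p̄)/161.9]
- SE1 = √[(p1(1 − p1) + p2(1 − p2))/161.9]
- P(reject) = Φ[(d − 1.96·SE0)/SE1] + Φ[(−d − 1.96·SE0)/SE1]

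For d = 0.03: SE0 = 0.0516 and SE1 = 0.0516, so Φ(−1.38) + Φ(−2.54) = 0.084 + 0.006, or about 0.089.

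| Assumed risks, no treatment effect | Two-sided rejection rate |
|---|---|
| 33% vs 33% | 5.0% |
| 33% vs 31% | 6.7% |
| 33% vs 30% | 8.9% |
| 33% vs 28% | 16.4% |
| 33% vs 25% | 35.4% |

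A beta-binomial simulation (40 clusters of 10, cluster-level t-test) agrees: 4.9% with equal risk, and 8.8%, 16.9% and 35.6% for imbalances of 3, 5 and 8 points.

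*Opposite direction.* Keep the planned relative effect, 0.20/0.33 = 0.606, and let intervention practices enrol patients at higher underlying risk.

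| Intervention arm's underlying risk | Its risk after effect | Power against 33% |
|---|---|---|
| 33% | 20.0% | 76% |
| 36% | 21.8% | 62% |
| 38% | 23.0% | 51% |

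**The case against.** The article does not say when a practice learns its arm. The call is between two coordinators, and what counts as definitive inclusion is not defined. A reader might infer that the plan states outright that practices recruit unblinded. It does not; that order is the likeliest reading.

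A reader might also infer that the plan admits a bias. The Discussion concedes a possibility, openly, and neither an actual bias nor that it was avoidable.

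It is tempting to say that intervention practices recruit people willing to attend a class while control practices recruit people willing to keep a diary. The text does not support that contrast. Both arms share one set of eligibility criteria, including the exclusion for inability to exercise, the same practice workshop, and the same visits at 0, 4, 12 and 24 months. Several qualifying criteria are timed or observed tests. These safeguards stand and should narrow the difference. They do not make recruitment blind, because any single criterion qualifies a patient and some rest on self-report or judgement.

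The sizes above rest on assumed imbalances and on a chi-square for fallers, whereas the primary analysis models fall counts. The plan itself treats the chi-square as a reasonable approximation, but the figures illustrate the risk and do not estimate it.

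Finally, covariate adjustment and sensitivity analyses are left to a statistical analysis plan that is not shown, so their absence from the article is not a fault.

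**Conclusion.** The point holds as a risk of differential recruitment. As described, nothing fixes a practice's patients before its arm can be known, and the reason given in the Discussion explains why individuals were not randomised but not why disclosure comes first. With no true effect, an assumed 3- or 5-point lower underlying fall risk in one arm would raise the two-sided error from 5% to about 9% or 16%. If intervention practices instead enrolled patients at 3 or 5 points higher risk, power would fall from about 76% to 62% or 51%. The documents do not indicate which direction is likelier, or whether any imbalance will occur.

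The conclusion rests on the inferred order of steps. If patients were in fact enrolled before disclosure, the concern would fall away and the article would only need to say so.

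**What to change.** **Practices not yet allocated.** Change the trigger. The practice screens, consents and baseline-tests its patients, closes its list and registers it. Only then does the other region's coordinator disclose the allocation, and no patient is added afterwards. The cross-region call and the sample size are unchanged.

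Month 0 must move with the trigger. Measurements sets baseline at inclusion, so time spent waiting for the list to close would otherwise count as untreated time in the intervention arm's 12-month window. The 12-month fall count and the 4-, 12- and 24-month visits should run from the date of disclosure in both arms.

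**Practices already allocated.** Adjust the primary negative binomial model for prior-year falls and baseline Timed-up-and-go, both already collected, unless the statistical analysis plan already does so. This is partial mitigation: it cannot correct selection on unmeasured traits. State the remaining risk as a limitation.

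**Cost.** A short amendment to the order of steps and to the definition of month 0. The first patients enrolled in a practice wait until its list closes, so their baseline tests are somewhat older at month 0 (in both arms), and trainer courses start slightly later. The wait will be longer where recruitment is slow.

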### Ethics

The study protocol was approved by the ethics board of the faculty of medicine of the Technische Universitaet Muenchen. The study design takes into account the principles set out in the Helsinki declaration (Seoul, 2008). All patients have to sign informed consent forms.

### Participating practices

General practitioners interested in participating in the trial are recruited from local peer groups (quality circles), from networks affiliated to the Institute for Family Medicine, Technische Universitaet Muenchen and the Institute of Sports Science and Sports, University Nuremberg/Erlangen as well as by advertising in medical journals. Participating physicians have to be licensed general practitioners working with elderly persons in a community dwelling setting. Physicians and one staff member (medical secretary, receptionist, assistant) of each participating practice in both experimental and control group are trained in workshops lasting 3.5 hours. The workshop introduces goals, methods and logistics of the study, provides background knowledge on falls (definitions, epidemiology and recommended guidelines) and includes a practical training part on the methods for fall risk assessment. For the attendance of the workshop physicians gain Continuing Medical Education (CME) points.

### Participating patients

The target population of the study are community-dwelling persons aged 65 years and older with a high risk of falls. To be included at least one of the following criteria has to be met (see section measurements for a detailed description of the tests): fall within the last 12 months, fear for falling [35], chair-stand-ups >10 sec. [36], Timed-up-and-go-Test >10 sec. [37,38], balance impairments measured by the three balance tests of the Guralnik short physical performance battery [36] or self-reported subjective balance deficits. Persons not living independently and patients suffering from physical or mental restrictions that do not allow participation in an exercise program or the assessment of risk of falling are excluded. Each participating practice is asked to recruit 10 to 15 patients. In case of problems with recruiting the regional coordinating team supports recruitment activities.

### Intervention

Physicians taking part in the study are asked to name a certified local physiotherapist or an university trained sport scientist interested to act as exercise instructor (trainer) for the fall prevention program. If the general practitioner cannot name a trainer the coordination team will identify a qualified person. If the practice is randomised to intervention program the study centre invites the trainer to a special course lasting 8 hours. The course covers the standardised evaluated intervention program [39-41] as well as other study-related issues such as definition of falls and assessment procedures to enable trainers to answer upcoming questions of the participants.

The intervention investigated in PreFalls is a 16 week program with focus on fall prevention. It is based on a program which has been successfully tested in a previous trial [40] but expanded by a fear of falling module. Briefly it contains a progressive strength and flexibility training, challenging balance, gait and motor coordination training and progressive endurance training (Table 1). Sessions take place once a week and last 60 minutes each. The multi-modal intervention focuses on the improvement of motor control with several components relevant for falls prevention: balance, gait, motor coordination in daily routine activities, and strength training. The intervention incorporates, both, group and home-based exercises as well as physical activity recommendations and educational components for fall prevention. The strength training includes progressive body weight-bearing exercise and functional power training. Balance training contains, for example, standing balance, dynamic weight transfers, stepping strategies. Gait training included walking with change of pace and direction. For daily activity performance, exercise included motor coordination under time pressure and sensory awareness. The exercise intervention also includes strategies for getting up from the floor. Given the importance of fear of falling, components of the "Matter of Balance" program [42] have been added to the intervention program to address not only physical but also psychological risk factors for falls. This cognitive behavioural program aims to reduce fear of falling by increasing self-efficacy. The evidence-based components of restructuring misconception of fall risk, attitudes about falls, as well as individual goal setting of changed behaviours for fall risk reduction are addressed [40,41].

**Table 1 T1:** Intervention Details

Component	Sessions	Percentage
Strength Training	5	11%
Training of Perception & Components of Motor Coordination	10	21%
Flexibility Training	6	13%
Endurance Training/Gait & Balance Training	5	30%
Fall Risk Education	5	11%
Home Programm	2	4%
Fear Avoidance	3	7%

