### Measurements

Table 2 provides an overview of the type and timing of measurements in PreFalls. Assessment visits take place at baseline (inclusion = month 0), at 4, 12 and 24 months. Falls are monitored by patients over the full study period with a daily fall calendar.

**Table 2 T2:** Study schedule

Month	0	4	12	24
Sociodemographic characteristics	X			
Weight, height	X	X	X	X
Morbidity, medication	X	X	X	X
				
Risk of Fall assessment (Timed "Up and Go" Test, Chair Rising test, Romberg-Test, Tandem and Semi-Tandem Stand)	X	X	X	X
				
EuroQol Quality of Life questionnaire	X	X	X	X
Falls Efficacy Scale (FES-I) questionnaire	X	X	X	X
PAR questionnaire for physical activity level	X	X	X	X
	XXXXXXXXXXXXXXXXXXXXX			
Fall diary				
				
Fall prevention program (intervention group only)	XXXXXXXXX			

For the full study period of 24 months participants are asked to fill in a fall diary. For each day they mark whether they fell or tripped. The monthly calendar is sent to the study coordinators during the first week of the following month in a prepaid envelope. When a fall occurs, detailed information is obtained through structured telephone interviews (see Table 3). If the diary is not received within 10 days after the end of the documented month the participant is contacted by phone. In case that during follow-up some patients stop to fill in the diary they will be phoned to ask for basic information on falls (number of falls, injuries and consequences).

**Table 3 T3:** Questions asked in the telephone interview after documentation of a fall in the diary

How often nearly fallen in the previous month?
How often fallen in the previous month?
Where did the last fall happen?
Getting up without help?
Time of fall?
Reason for falling?
Injuries?
Doctor consultation?
Which doctor consulted?
Admission to hospital?
Kind of shoes at time of fall?
Used glasses at time of fall?

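### Trainers, who exist only in the intervention arm, are prepared to answer participants' questions on the fall definition, so reporting of the self-recorded primary outcome may differ by arm

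*Protocol article*

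**What the plan says.** **The trainer's role.** The Intervention section of the protocol article says: "If the practice is randomised to intervention program the study centre invites the trainer to a special course lasting 8 hours". Besides the exercise program, the course covers other matters related to the study, among them "definition of falls and assessment procedures to enable trainers to answer upcoming questions of the participants". On contact with patients the same section says: "Sessions take place once a week and last 60 minutes each". The program runs for 16 weeks, and Table 2 restricts it to the intervention group. Table 1 lists five sessions of fall risk education (11%). It lists no component on the outcome definition or on completing the diary.

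**The outcome.** The primary endpoint (Statistics) is the number of falls per individual over 12 months. Under Measurements, participants in both arms keep a daily diary: "For each day they mark whether they fell or tripped". A calendar is returned each month, a late one prompts a telephone call, and a documented fall prompts a structured interview (Table 3). Participants who stop the diary are telephoned for basic information on falls. Objectives gives one definition of a fall for the whole study.

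**What both arms share.** Under Participating practices, physicians and one staff member "of each participating practice in both experimental and control group are trained in workshops lasting 3.5 hours", and the workshop includes definitions of falls.

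**The concern.** The diary asks a patient to separate a fall from a trip. Anyone who helps the patient draw that line can change the count. The plan gives such a helper an explicit question-answering task in one arm only. It lists the task apart from the exercise program, so the task is not part of the treatment under test and need not differ by arm. Patients cannot be unaware of whether they attend the program.

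If the extra guidance changes what intervention patients record, the rate ratio mixes a change in falls with a change in recording. No model can separate the two afterwards, because the trial has no independent count of falls. The plan itself regards incomplete reporting as a problem in this population: Background says that "it is likely that there is a considerable underreporting of falls".

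**Working it through.** The documents give no reporting rates, and the plan has no figure on this point to reproduce. The check therefore compares the two arms and then illustrates the possible size with assumed rates.

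**1. Sources of guidance by arm**

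| Source | Intervention | Control |
|---|---|---|
| Practice physician and staff member taught fall definitions | yes | yes |
| Same diary, monthly return, reminder call, interview | yes | yes |
| Trainer met weekly for 16 weeks, prepared to answer definition questions | yes | no |

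Only the last row differs. The practice training is the same in both arms, so it does not offset the trainer. The article also gives practice staff no stated task of answering diary questions. Scheduled assessments are at months 0, 4, 12 and 24, so none lies between baseline and month 4.

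**2. What the interview can catch.** Table 3 asks separately about near-falls and falls, so a trip recorded as a fall may be corrected. The interview follows a fall documented in the diary, so a fall left out or marked as a trip, in a month with no documented fall, is not checked this way.

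**3. Effect on the rate ratio.** Observed ratio = true ratio × (share of falls recorded, intervention) / (share recorded, control). Assumed: true ratio 0.70, control share 80%.

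- Shift lasting the whole year:
  - 90% in the intervention arm: 0.70 × 0.90/0.80 = 0.79.
  - 85% in the intervention arm: 0.70 × 0.85/0.80 = 0.74.
- Shift lasting only the 16 weeks, with falls spread evenly (16/52 = 0.308 of the year):
  - 90%: 0.70 × (0.308 × 0.90 + 0.692 × 0.80)/0.80 = 0.73.
  - 85%: 0.70 × (0.308 × 0.85 + 0.692 × 0.80)/0.80 = 0.71.
- Opposite direction, with 10% relatively less recording in the intervention arm all year: 0.70 × 0.90 = 0.63.

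**4. Effect on the test, on the scale of the sample size section.** Inputs from that section: 33% against 20% with at least one fall, 382 patients, cluster size 10, intra-cluster correlation 0.02, two-sided 5%. The design effect is 1 + 9 × 0.02 = 1.18, so the effective number per arm is 191/1.18 = 161.9. The standard two-proportion formula then gives 75.7% power. The plan states 80%, from simulation software whose settings are not shown; 75.7% serves here only as the baseline. Assumed relative shifts in the intervention arm's recorded proportion give:

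| Shift | Recorded proportion | Power |
|---|---|---|
| none | 0.20 | 75.7% |
| +10% | 0.22 | 60% |
| +20% | 0.24 | 43% |
| −10% | 0.18 | 88% |
| −20% | 0.16 | 95% |

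With no true effect (33% in both arms), the two-sided rejection probability is 5% without a shift, about 6% with a 5% shift, 9.5% to 9.8% with a 10% shift and 23% to 25% with a 20% shift, the ranges covering the two directions.

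**The case against.** The strongest case against is that formal ascertainment is the same in both arms: one definition, one diary, one reminder rule, one interview. Control patients also have a contact in their own practice who has been taught fall definitions. That stands, and it rules out two stronger readings: that the outcome is in fact ascertained differently by arm, and that control patients have nobody to ask. The difference is one additional and more frequent contact.

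A reader might also infer that intervention patients are coached each week on what counts as a fall. The text does not say so. Trainers answer questions that come up, and Table 1 has no such component.

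The direction of bias is open too. Better knowledge of the definition could raise recording, which moves the ratio towards no effect, or lead patients to leave out trips and near-falls, which moves it towards benefit. The gap in the interview noted above bears on omitted falls, but that does not settle the direction. The remark on underreporting in Background concerns published prevalence, not a prospective daily diary with telephone follow-up, so it lends only general support.

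Finally, fall-risk education belongs to the intervention and will raise awareness of falls in that arm whatever the trainers' other role. The gain from the change may therefore be small. That stands, and it limits the severity.

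**Conclusion.** The concern holds as a minor one. The plan states an avoidable asymmetry: one arm has an extra, regular contact prepared to give guidance on the definition behind an unblinded, self-reported primary outcome. It creates a risk of differential reporting; it does not show that such reporting will occur.

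Size and direction are unknown. The ratios of 0.79 (all year) and about 0.73 (16 weeks only) against a true 0.70 rest on assumed recording of 90% and 80%. The shorter case also assumes that falls are spread evenly and that the effect on recording ends with the program. The power figures rest on assumed shifts as well.

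A reader might infer that a comparison of first-year with second-year falls would be distorted. The article lists second-year falls as a secondary outcome but plans no contrast between the years, so that claim is not supported. Whether the calendar already prints the definition cannot be judged from a condensed article. The point therefore rests on the trainers' role alone.

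**What to change.** State in the trainer course that trainers do not answer questions on the diary or on what counts as a fall, and that they refer these to the regional study coordinators. The coordinators already receive the calendars. They should answer such questions from both arms with one standard script. Give both arms the same written definition, as worded under Objectives, with the diary, if this is not already done. Leave the exercise and fall-risk education content unchanged.

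The cost is a sentence in the course material, a short script and a few more calls to the coordinators. The change has to be in place before falls are recorded, since it cannot be made in the analysis. Greater fall awareness from the education sessions will remain in one arm and should be acknowledged as a limitation when the results are reported.
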